## Abstract

**Background:**

Clinical decision support systems (CDSS) are low-cost, scalable tools with the potential to improve guideline-based antihypertensive treatment in primary care, but their effectiveness needs to be tested, especially in low- and middle-income countries such as China.

**Methods:**

The Learning Implementation of Guideline-based decision support system for Hypertension Treatment (LIGHT) trial is a pragmatic, four-stage, cluster-randomized trial conducted in 94 primary care sites in China. For each city-based stage, sites are randomly assigned to either implementation of the CDSS for hypertension management (which guides doctors’ treatment recommendations based on measured blood pressure and patient characteristics), or usual care. Patients are enrolled during the first 3 months after site randomization and followed for 9 months. The primary outcome is the proportion of hypertension management visits at which guideline-based treatment is provided.

In a nested trial conducted within the CDSS, with the patient as the unit of randomization, the LIGHT-ACD trial, patients are randomized to receive different initial mono- or dual-antihypertensive therapy. The primary outcome of the LIGHT-ACD trial is the changes in blood pressure.

**Discussion:**

The LIGHT trial will provide evidence on the effectiveness of a CDSS for improving guideline adherence for hypertension management in primary care in China. The nested trial, the LIGHT-ACD trial, will provide data on the effect of different initial antihypertensive regimens for blood pressure management in this setting.

**Trial registration:**

ClinicalTrials.gov, identifier: LIGHT (NCT03636334) and LIGHT-ACD (NCT03587103). Registered on 3 July 2018.

**Supplementary Information:**

The online version contains supplementary material available at 10.1186/s13063-022-06374-x.

## Introduction

Hypertension is the leading modifiable risk factor for death globally [1]. Over the past decades, the number of individuals with hypertension is estimated to have increased by 90%, with the majority of the increase occurring in low- and middle-income countries (LMICs) [2]. In China, an estimated 244.5 million adults have hypertension, and only about 15% of these individuals have adequate blood pressure control, resulting in major health and economic burdens [3].

Improving the performance of primary care doctors, who play a key role in managing hypertension, and ensuring their adherence to guideline-recommended antihypertensive treatments are public health priorities in China [4]. Despite the decade-long efforts to strengthen the primary care system [5], the underuse of guideline-based antihypertensive treatments persists [6–8]. Moreover, given the substantial gaps in the licensure and education of primary care doctors [9], traditional strategies to empower their practices including educational training are resource-intensive to implement and may only yield modest effects [10]. A clinical decision support system (CDSS), characterized by generating recommendations through computerized algorithms, may circumvent these barriers to adequate management of hypertension [4, 11]. However, evidence of CDSS enhancing guideline adherent prescribing in hypertension is limited, especially in LMICs [12, 13]. Most studies have focused on assessing its effect on blood pressure reduction and have shown mixed results [14–16]. Understanding the effectiveness of CDSS for hypertension management in primary care could provide important information to develop effective strategies for mitigating the burden of hypertension in China and other LMICs.

In addition, in the course of testing the CDSS, there is an opportunity to test different antihypertensive regimens. Blood pressure guidelines endorse these antihypertensive therapies as equivalent even though there is a paucity of head-to-head comparisons [17, 18]. Using the CDSS to promote guideline adherence may facilitate such comparisons since randomization of treatment can be performed within the CDSS each time a decision support recommendation is generated for the patient. Nesting a randomized trial comparing antihypertensive regimens within CDSS will optimize the conduct and efficiency of the nested trial by streamlining the enrolment and follow-up.

Accordingly, our main aim is to conduct a cluster-randomized controlled trial, the Learning Implementation of Guideline-based decision support system for Hypertension Treatment (LIGHT) trial, to assess the effectiveness of a CDSS on improving guideline-concordant antihypertensive treatment and blood pressure control compared to usual care. Within the LIGHT trial, we also conduct a nested trial, the LIGHT-ACD trial, to compare blood pressure changes between different initial guideline-recommended drug regimens.

## Methods

### The LIGHT trial

#### Objectives

The primary objective of the LIGHT trial is to determine whether CDSS is effective in improving the use of guideline-based antihypertensive treatment compared to usual care, and the secondary objectives are to determine its effect on blood pressure changes and blood pressure control.

#### Trial design and setting

The LIGHT trial is a pragmatic, parallel-group, four-stage, cluster-randomized controlled trial assessing the effectiveness of CDSS in primary care in China, with primary care sites (including community health centers, community health stations, and township health centers) as the unit of randomization. In each stage, urban primary care sites are randomized to either implementation of the CDSS for hypertension management or usual care (Fig. 1). During the first 3 months after cluster randomization, patients who attend the clinic for hypertension management are screened for eligibility and if eligible asked to attend the clinic at least every 3 months with data collected at each visit (Fig. 2).

**Fig. 1 Fig1:**
[figure not shown]
Infrastructure of the LIGHT and LIGHT-ACD trials

**Fig. 2 Fig2:**
[figure not shown]
Schedule of enrollment, intervention allocation and assessment of the LIGHT trial using Standard Protocol Items: Recommendations for Interventional Trials (SPIRIT)

#### Eligibility criteria

In each city-based stage, local coordination centers of the trial invite all primary care sites in their network to participate in the trial. Primary care sites with hypertension clinics are eligible to be included if (1) at least one agent from each of the four classes of antihypertensive medication is available for the prescription [angiotensin-converting enzyme inhibitors (ACEI)/angiotensin receptor blockers (ARB), beta-blockers, calcium channel blockers (CCB), diuretics]; (2) an electronic health record (EHR) is being used for hypertension management providing a structured template for collection of patient data; and (3) at least 100 patients with hypertension are routinely being seen. Cluster drop-out is not expected but might occur if sites voluntarily withdraw during the trial.

Residents aged ≥18 years registered for hypertension treatment at the primary care sites are eligible for the LIGHT trial if they are taking 0–2 classes of antihypertensive medication. Major exclusion criteria include (1) history of coronary heart disease, heart failure, or chronic kidney disease; or (2) intolerance to 2 or more classes of antihypertensive medications; (3) systolic blood pressure (SBP) ≥180 mmHg or diastolic blood pressure (DBP) ≥110 mmHg at the screening visit (see detailed inclusion and exclusion criteria in Table 1). The screening of patients can be automatically performed by the customized EHR. As the informed consent for implementing the CDSS is waived in this trial, doctors can check the eligibility of all patients attending their clinics for hypertension management.

**Table 1 Tab1:** Inclusion and exclusion criteria of participants for LIGHT and LIGHT-ACD trials

Criteria	LIGHT	LIGHT-ACD
**Inclusion**	Residents aged ≥18 years registered for hypertension treatment at primary care sites	Participants from intervention sites of LIGHT study with systolic blood pressure ≥140 mmHg at the screening visit
	Taking 0–2 classes of antihypertensive medications	Not taking antihypertensive medication or taking only one which was not beta-blocker
**Exclusion**	History of coronary heart disease^a^, heart failure, and chronic kidney disease	Known/diagnosed diabetes mellitus
	Intolerance to 2 or more classes of antihypertensive medications	Intolerance to 1 or more classes of antihypertensive medications
	Secondary hypertension (physician-diagnosed)	Home blood pressure (if available) below 135/85 mmHg
	Systolic blood pressure ≥180 mmHg or diastolic blood pressure ≥110 mmHg at the screening visit	
	Serious medical conditions (e.g., malignant cancer and hepatic dysfunction)	
	Currently in an acute episode of disease	
	Currently pregnant or breastfeeding, or planning a pregnant or breastfeeding during the study	
	Cognitive or communication disorders	

^a^ Including angina, myocardial infarction, coronary artery bypass grafting, percutaneous coronary intervention, >50% stenosis of coronary artery, or positive stress test

#### Allocation

Primary care sites selected are randomized to intervention or control arm (1:1 ratio) using computer-generated random numbers stratified by baseline appropriate antihypertensive treatment rate and site characteristics (see detailed stratifying factors for each stage in Supplement 1). Site randomization is performed centrally, and participating sites will be confirmed by local coordinating centers before randomization. The statistician assigns sites to the randomization strata and uses a computer program to randomly allocate half the sites in each strata to the intervention group; the remaining sites are allocated to the control group. Group allocation is unknown to any other team member before a formal announcement to the investigators and sites. Given the nature of the intervention, doctors and participants cannot be blinded. Data analysts will follow a predefined analysis plan to avoid bias.

#### Intervention

The intervention consists of an EHR-based CDSS providing antihypertensive recommendations generated from information recorded at the visit. The recommendations are based on the Chinese primary care hypertension guidelines [19] but are generally consistent with international guidance [20, 21] and include treatment advice to add one or more of the 4 classes of medication at half or full dose (see an example of CDSS recommendation in Supplement 3). During prescribing, the dosages and frequencies of drugs can be filled in automatically according to the specific agents entered by doctors. To ensure that the intervention is being reliably delivered to doctors, clicking the icon for obtaining CDSS recommendations is designed to be mandatory before prescribing in the EHR. If the doctor decides not to follow the recommendation, a pop-up message stating “your prescription did not match with CDSS recommendation, please re-evaluate the classes/doses/frequencies of drugs.” and prescriptions can be modified accordingly. If the doctor decides not to follow the CDSS recommendation, relevant reasons (e.g., doctor preference or patient refusal) are recorded. In addition, if prescriptions involve contraindicated drugs, under-dosage, or over-dosage, a message warning is also triggered.

The CDSS algorithm was developed by clinicians in the research team based on guidelines for hypertension management [19–21]. After the algorithm was finalized, our information technology (IT) team translated it into computational logic. The logic of the CDSS was tested using simulated patient data to trigger each possibility. The CDSS was further validated by comparing the treatment recommendations provided by CDSS with that by clinicians for specific test cases. The IT team was notified when any discrepancies were found so that the programming errors could be identified. This process was repeated until no errors were observed in all test cases. The CDSS was piloted in two excluded sites. During the pilot test, there were a total of 78 hypertension visits. The mean SBP and DBP were 131.5 mmHg and 76.6 mmHg, respectively. Doctors followed the CDSS recommendations in 52.6% of hypertension visits. The most common reason for the non-compliance was patient refused to follow even though such recommendations had been provided by doctors in the shared decision process (83.8%).

After randomization, doctors in the intervention sites receive face-to-face or online training on the use and interpretation of the CDSS output. In addition, the evidence base of the output is briefly introduced. After the training, the IT team releases a new version of EHR with CDSS available for the intervention sites, doctors are instructed to use the CDSS directly in all hypertension visits thereafter.

#### Control

In control sites, the EHR is used to record the same information, but no antihypertensive recommendation is made. Prescribing decisions are made by doctors based on their knowledge and usual practice.

#### Outcomes

The primary outcome for the LIGHT trial is the proportion of hypertension visits (see Supplement 2 for specification) during which appropriate antihypertensive treatment is prescribed. Appropriate antihypertensive treatment is defined as a prescription compliant with the pre-specified guideline-based recommendations (see Supplement 4 for specifications). The secondary outcomes include the average change in systolic blood pressure, the proportion of those whose blood pressure is controlled at 9 months, and the proportion of hypertension visits with *acceptable* antihypertensive treatment, which is defined as either appropriate antihypertensive treatment (as above) or those treatments with acceptable reasons for failing to titrate antihypertensive treatment. An exploratory outcome is the number of patients experiencing a vascular event defined as a composite of cardiac death, non-fatal stroke, and non-fatal myocardial infarction (Table 2).

**Table 2 Tab2:** Outcomes of LIGHT and LIGHT-ACD trials

Outcomes	LIGHT	LIGHT-ACD
**Primary**	Appropriate (guideline-based) antihypertensive treatment rate	Absolute change in blood pressure at 9 months of different regimens of initial therapy
**Secondary**	Absolute change of systolic blood pressure at 9 months	Proportion of individuals with blood pressure controlled (SBP <140 mmHg and DBP <90 mmHg) at 9 months
	Blood pressure control rate (defined as SBP <140 mmHg and DBP <90 mmHg) at 9 months	Proportion of individuals with SBP <160 mmHg and DBP <100 mmHg at 9 months
	Acceptable (appropriate/non-appropriate but with proper reasons) antihypertensive treatment rate	Proportion of individuals who received monotherapy^a^, dual therapy, triple therapy, and referral at 9 months
		Proportion of individuals with antihypertensive drug side-effects
		Proportion of individuals transferred to usual care for any reason
**Exploratory**	A composite of cardiac death, non-fatal stroke, and non-fatal myocardial infarction	Absolute change in blood pressure at 9 months of different protocols^a^

Primary and secondary outcomes of LIGHT-ACD were assessed among initiating therapies; exploratory outcomes of LIGHT-ACD were assessed among protocols

*SBP* systolic blood pressure, *DBP* diastolic blood pressure

^a^ Only assessed in Population 1, who are not currently taking any antihypertensive medication with systolic blood pressure 140–159 mmHg, and initiated with monotherapy

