#### Statistical analysis

The analyses and reporting of the results will follow the Consolidated Standards of Reporting Trials guidelines for cluster-randomized controlled trials [25]. All the analyses will be performed on an intention-to-treat basis. Multiple imputations by chained equations will be used to account for missing values.

With all comparative outcomes, we will use mixed-effects generalized linear regression models, using logistic or linear response for dichotomous or continuous outcomes, respectively, and including a random effect for the study site. Implementation stages will be treated as strata, with adjustment for calendar time to account for secular trends. The consistency of treatment effects on the primary outcome will be explored in predefined subgroups, including age, gender, education, implementation stage, tertiles of baseline cluster-level appropriate treatment rate, blood pressure level, and use of antihypertensive medications. All statistical tests will be performed using 2-sided tests at the 0.05 level of significance, but the number of tests and *p*-value will be taken into account in the interpretation of the results.

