Third, the pragmatic design of both trials enables us to demonstrate the real-world effectiveness of intervention/treatment with greater external validity [36, 37]. In contrast to trials with study-specific visits, the enrolment and follow-up of patients, and the collection of outcome data in our trial are incorporated into routine clinical practice. Furthermore, the exclusion criteria are kept to a minimum to enroll a diverse spectrum of the population. These considerations improve the efficiency of trials and enhance the generalizability of the study results [37].

Fourth, the two studies are further distinguished by the efforts to build a learning decision support tool. Although the algorithm of CDSS is kept consistent during the four stages of the trial, it has the potential to be adaptively updated after the results of the LIGHT-ACD trial are available. For the ultimate implementation of the CDSS, the tool could continuously generate new knowledge in terms of the effectiveness of treatment strategies from the ongoing delivery of care, whereby the CDSS could be iteratively tested and improved by shifting the randomization ratio of stepped antihypertensive protocols toward the more effective group [38].

Our study has some potential limitations. First, the outcomes are focused on surrogate outcomes and not clinical outcomes such as cardiovascular events. To examine the effect on clinical events, a much longer trial would be required. However, it is expected that improvements in blood pressure control over time would favorably affect clinical outcomes. Second, given the nature of the CDSS, which delivers its recommendation directly to doctors, blinding was not feasible. We minimized the potential bias by using objective measures as primary and secondary outcomes. Third, due to the limited timeframe of the study, an extended follow-up was not included following the intervention to measure the persistence of effects after the intervention ceases. Fourth, we did not include consideration of diet, in part because of issues of the validity of self-reporting. In this trial, we only collected information necessary for pharmacological hypertension management such as the blood pressure measurements, comorbidities, current medications, and prescriptions. However, the confounding effect of diet may have been minimized through site randomization.

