### Trial status

Protocol version 4.4 commenced on December 28, 2020. As of May 2021, 94 sites (including 7,656 patients in LIGHT and 494 participants in the LIGHT-ACD trial) have been randomized in 4 stages. Site randomization of Stage 1 was on 21 August 2019, Stage 2 on 4 December 2019, Stage 3 on 1 March 2021, and Stage 4 on 14 April 2021. The implementation of the trial is affected by the outbreak of COVID-19, we have extended the enrolment and follow-up periods appropriately in each stage of the trial. Currently, all sites will complete follow-up by the middle of 2022.

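### Read literally, LIGHT's exploratory vascular-event composite counts fatal myocardial infarction but not fatal stroke

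*Protocol article*

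**What the plan says.** Under The LIGHT trial, Outcomes, the article lists one exploratory outcome, for vascular events, which is "defined as a composite of cardiac death, non-fatal stroke, and non-fatal myocardial infarction". Table 2 (Exploratory row, LIGHT column) gives the same three components. The unit is the patient: what is counted is "the number of patients experiencing a vascular event".

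The Statistical analysis section for LIGHT applies mixed-effects models to all comparative outcomes, "using logistic or linear response for dichotomous or continuous outcomes, respectively, and including a random effect for the study site". A yes/no vascular event per patient would therefore go into the logistic version. Follow-up is short: "Patients are enrolled during the first 3 months after site randomization and followed for 9 months".

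The article does not define cardiac death. It lists no vascular or all-cause death outcome for LIGHT and gives no rule for how a stroke death enters this count.

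**The concern.** The label and the component list do not match. A fatal stroke is a vascular event in any ordinary sense, yet it fits none of the three components. The rule also treats the two named diseases unequally: myocardial infarction counts whether or not the patient survives (as cardiac death or as non-fatal infarction), whereas stroke counts only if survived.

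The composite is exploratory, but it is the only outcome listed for LIGHT that compares serious clinical events between arms. Prior stroke is not among the exclusions in Table 1, while coronary heart disease and heart failure are, so stroke may well make up a good part of the events. Events will probably be few, and dropping the most severe form of one component loses information the trial can ill spare.

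**Working it through.** **1. Component check.** Each event type is set against the list in Outcomes and Table 2, taking a patient with that event only.

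| Event | Component it fits | Counted? |
|---|---|---|
| Fatal myocardial infarction | cardiac death | yes |
| Non-fatal myocardial infarction | non-fatal myocardial infarction | yes |
| Non-fatal stroke | non-fatal stroke | yes |
| Fatal stroke | none | no |

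A patient who dies of stroke after an earlier counted event stays counted, because the outcome is per patient.

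**2. Is there a plan figure to reproduce?** No. The article gives no event rate, case fatality, sample size or power for this composite. The steps below are illustrations on stated assumptions.

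**3. Under-count.** Let S be the strokes in an arm (one per patient) and f the fraction fatal within follow-up. Strokes counted = S × (1 − f), so the share lost is f.

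- S: Trial status reports "94 sites (including 7,656 patients in LIGHT and 494 participants in the LIGHT-ACD trial) have been randomized in 4 stages". An even split (assumption) gives 7,656 / 2 = 3,828 patients per arm. A 1% stroke rate (assumption) gives S = 38.3.
- f = 10%: 38.3 × 0.90 = 34.5 counted, 3.8 lost.
- f = 30%: 38.3 × 0.70 = 26.8 counted, 11.5 lost.

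The share lost does not depend on the stroke rate.

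**4. Between-arm comparison.** With equal stroke incidence in arms A and B, the apparent ratio B/A for the stroke component is (1 − fB) / (1 − fA).

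- Equal case fatality, 10% in both arms: 0.90 / 0.90 = 1.00. There is no directional bias.
- 10% in A, 20% in B: 0.80 / 0.90 = 0.89.
- 10% in A, 30% in B: 0.70 / 0.90 = 0.78.

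**5. Dilution in the composite.** Suppose cardiac deaths plus non-fatal infarctions equal total strokes in each arm (assumption). The composite ratio is then (1 − fB + 1) / (1 − fA + 1).

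- 10% against 20%: 1.80 / 1.90 = 0.95.
- 10% against 30%: 1.70 / 1.90 = 0.89.

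**6. Against chance.** For counts of 34.5 and 26.8, the standard error of the log ratio is √(1/34.5 + 1/26.8) = 0.258. The approximate 95% interval around 0.78 is 0.47 to 1.29, before any widening for clustering by site.

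**7. After the fix.** With fatal strokes counted, both arms contribute S strokes, and the stroke-component ratio is 1.00 in every scenario in step 4.

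**The case against.** The strongest reply is that little rests on this outcome. It is labelled exploratory and the LIGHT sample size does not address it. The Discussion says plainly: "To examine the effect on clinical events, a much longer trial would be required". The article's conclusion does not rely on it. All of this stands, and it sets the weight of the point.

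A second reply is that an article condenses. The full protocol may define cardiac death to include stroke death, or may count a stroke that was survived for some time before death. The text and Table 2 are also not independent confirmations, since the sentence refers to the table. This stands as a limit on certainty about intent. It does not clear the article, which prints an explicit component list; if the full protocol is broader, the printed list still needs correcting.

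A reader might go further and infer that the arm with deadlier strokes will look better. The documents do not support this. It needs stroke case fatality to differ between arms, and the article offers no mechanism by which prescribing support would produce such a difference over 9 months. The ratio of 0.78 puts the two ends of an assumed range in opposite arms and concerns strokes alone. The composite figure is nearer 0.89 under the assumption in step 5, and step 6 shows that even 0.78 would lie well within chance.

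**Conclusion.** The point holds as a definitional error in an exploratory outcome. As printed, the composite misses patients whose only event is a fatal stroke, although it counts fatal myocardial infarction and is called a vascular event. The certain effect is an under-count in both arms, by 10% to 30% of strokes if that share is fatal within follow-up. That range is an assumption, not a figure from the article.

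Bias between arms is conditional on case fatality differing by arm, and there is no evidence that it will. A reader should not infer that LIGHT's main findings are at risk: the primary outcome and the secondary outcomes (blood pressure and acceptable treatment) do not use this composite. The conclusion also rests on the ordinary meaning of cardiac death, which the article leaves undefined.

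**What to change.** In the Outcomes text and in the Exploratory row of Table 2, replace the cardiac death component with *cardiovascular death (including fatal stroke)*, leaving the other two components as they are. Alternatively, keep cardiac death and count stroke whether fatal or non-fatal. Either closes the gap; the first also brings in other vascular deaths, which suits the label. If the full protocol already uses a broader definition, correct the article's wording to match. The change should be recorded before the outcome is compared by arm.

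The cost is one phrase in two places, plus classifying the few deaths as cardiovascular or not instead of cardiac or not. Table 3 lists hospitalizations and adverse events but does not name deaths, so the route by which deaths and their causes are recorded should be confirmed. Scoring cardiac death already requires a cause of death, so the extra work should be slight.
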